### 6.3 RANDOMISATION, ENROLMENT AND MASKING

Participants will be randomised at a 1:1:1 ratio to I-BA (guided, self-guided internet-delivered behavioral activation) and a control condition (TAU for depression within CAMHS or pediatric primary care). Randomisation is planned to occur as soon as possible after the diagnostic assessment visit, and never later than 1 month after this visit.

Randomisation will be set up and monitored by the Karolinska Trial Alliance (KTA) using an online randomisation service (ALEA). Randomly varying block sizes of six and nine will be generated using a computer random number generator. We will stratify by two sites, to enable for inclusion of an extra site later on in the trial.

The trial coordinator or co-coordinator will be responsible for enrolment of participants and assigning participants to therapists. Participants will be informed that they will be allocated to one of three arms in the study.

Assessors conducting post- and follow-up assessments will be blind to treatment allocation, until the last follow-up (12FU). The outcome measures are identical for both groups, ensuring that the assessors remain blind. At each follow-up assessment, participants will be reminded by their assessor to not reveal their arm allocation. To measure blinding integrity, all assessors will record whether the participating families inadvertently reveal their group allocation, and subsequently guess each participant's treatment allocation at each assessment point and motivate their choice. The blinding will be broken after the trial's final participant has finished his/her 3-month follow-up assessment (primary endpoint). Blinding of individual participants will be kept for blind assessors until the 12-month follow-up assessment. The trial will end when the trial's final participant has finished his/her 12-month follow-up assessment.

In case of a medical emergency, we will refer participants to appropriate health care. The trial coordinator will be in charge of following up the incident. This whole procedure can be done without unblinding the outcome assessors, so an emergency unblinding system is not required for the trial.

## **6.4 TREATMENT**

### **6.4.1 GUIDED AND SELF-GUIDED I-BA**

The intervention arms consist of internet-delivered BA with (guided) and without therapist-support (self-guided) and involve both the adolescent and their caregiver. The adolescent and the caregiver are provided with their own separate programs and login to the platform.

Each of the I-BA interventions consists of 8 modules, delivered over a maximum of 10 weeks. In certain circumstances (e.g., illness or holidays), participants in guided ICBT can pause their therapist-support for one or two weeks. After 10 weeks, all modules will be made available for the participant (regardless of how many modules s/he has completed). The adolescent and caregiver can continue to access all treatment modules for the whole follow-up period (3 months), but without therapist-support.

During guided I-BA, participants have regular contact with a trained therapist inside the platform. The therapist provides feedback, answer questions, and reminds you to complete the next module if required. Communication is possible via traditional text messages (resembling e-mail) or via comments on specific worksheets. When the participant receives a message on the platform, s/he also gets an SMS reminder to her/his phone. The therapist usually logs in daily (on workdays; at minimum every 48 hours). Therapist time is automatically logged in to the platform. Participants are typically in contact with their therapist several times a week. Phone calls are possible if the participant/therapist for a certain reason feels it is needed but are generally kept to a minimum. The participants are welcome to contact their therapist at any time, who will reply during office hours.

An overview of the treatment is presented in **Table 1**. The treatment manual, developed by [name], consists of evidence-based interventions adapted to an online format inspired by previously published treatment manuals on behavioral activation for adolescents (36, 53). The main goal of the BA is to increase engagement in values-based activities and decrease avoidant behaviors that serve to maintain depression. The adolescent will learn about depression, how behavioral activations works, monitor their own activities, plan and do more values-based activities and deal with obstacles to getting in touch with positive reinforcement, such as avoidance behaviors.

The adolescents will also learn about common sleep problems in depression and how they can improve their sleep. Sleep disturbances commonly co-occur with depression in adolescents (54). However, research on this area is lagging behind and the Board of Health and Welfare provides no guidelines for treatment of insomnia when co-occurring with depression (55). The British National Institute for Health and Care Excellence's (NICE) guidelines for treatment of depression states that patients with sleep problems in depression should be offered advice on sleep hygiene (56). Therefore, we decided to include brief psychoeducation on sleep problems and advice on adaptive sleep behaviors (e.g., keeping regular sleep hours) early in treatment, to enable continuous work with establishing better sleep routines during the rest of the treatment.

The self-guided I-BA is identical to the guided I-BA intervention, however without therapist support. To ensure patient-safety, there will be clear instructions to the patients and primary caregivers how to get in contact with the study team in case of acute problems, and there will be clinical routines to detect and manage deterioration or suicidal tendencies.

We included a caregiver program in I-BA because caregivers are a significant part of the adolescents' daily life and can provide support with treatment assignments. Caregivers may also be part of an ineffective communication pattern that contributes to maintained depression. Involving caregivers facilitates modification of these unhelpful patterns. Caregivers are also commonly engaged in other BA-protocols for adolescents (53, 57). The caregiver program is consistent with principles from Parent Management Training (PMT; (58, 59), that teach caregivers positive parenting skills, aiming at strengthening the relationship between caregivers and their children.

The caregiver program consists of 8 modules, including psychoeducation about depression, how to support their adolescent suffering from depression, reviews of the content in the adolescent program, caregiver coping strategies, collaborative problem-solving and effective communication skills. Both the adolescent and the caregiver in guided I-BA have individual access to the same therapist. See **Table 1** below for more details on the treatment content.

**Table 1.** Treatment overview of I-BA

| Module | Adolescent                                                                                                                                                                                                                           | Caregiver                                                                                                                                                                                                                                                                       |
|--------|--------------------------------------------------------------------------------------------------------------------------------------------------------------------------------------------------------------------------------------|---------------------------------------------------------------------------------------------------------------------------------------------------------------------------------------------------------------------------------------------------------------------------------|
| 1      | Introduction to I-BA. Psychoeducation on depression. Rationale for BA. Homework: activity monitoring.                                                                                                                         | Introduction to I-BA. Psychoeducation on depression. Rationale for BA. Learn about common parental traps . Homework: notice one's parental behaviors when the adolescent shows depressive behaviors. Discuss with the adolescent how to collaborate in treatment. |
| 2      | Values assessment. Set treatment goals. Homework: activity scheduling.                                                                                                                                                        | Facilitate and encourage values-based activation; communication skills I: validate your child's feelings . Homework: practice validating others' and your child's emotions, encourage values-based activation.                                             |
| 3      | Continued values-based activation . Psychoeducation on sleep . Homework: activity scheduling and sleep hygiene.                                                                                                 | Spending positive time with your adolescent. Homework: suggest positive time with your adolescent.                                                                                                                                                                |
| 4      | Continued values-based activation . Identify and overcome barriers to activation through identifying and overcoming avoidance . Homework: activity scheduling, sleep hygiene and practice overcoming avoidance. | Communication skills II: How to avoid and manage conflicts . Homework: practice conflict management.                                                                                                                                                              |
| 5      | Continued values-based activation . Overcome barriers to activation through shifting focus to the present situation . Homework: activity scheduling, sleep hygiene and practice shifting focus.                 | Take care of yourself as a caregiver supporting a child with depression. Homework: take care of yourself.                                                                                                                                                         |
| 6      | Continued values-based activation . Problem solving . Homework: activity scheduling, sleep hygiene and problem-solving practice.                                                                                | Collaborative problem-solving . Homework: practice collaborative problem-solving                                                                                                                                                                                  |
| 7      | Putting it all together . Homework: activity scheduling.                                                                                                                                                               | Putting it all together . Homework: choose two tasks from previously introduced skills.                                                                                                                                                                           |
| 8      | Treatment summary. Relapse prevention . Make an evaluation of the treatment.                                                                                                                                                  | Course summary. Relapse prevention . Make an evaluation of treatment.                                                                                                                                                                                                    |

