#### **Quick Inventory of Depressive Symptomatology – Adolescent version (QIDS-A17)**

The QIDS-A17 (49) covers the nine DSM-5 symptoms of depression rated in a scale from 0 (none) to 3 (highest) with a sum-range of 0-27 [46]. A total score of 6-10 indicates mild depression, 11-15 moderate, 16-20 severe and 21 and above very severe. Response is defined as a reduction by half of the initial score on QIDS-A17-C. Remission is defined as below 6 points on QIDS-A17-C. The QIDS-A17 is a very reliable measure and most discriminating at moderate levels of depression(49).

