### **6.5 SUBSEQUENT ASSESSMENTS**

#### **6.5.1 ASSESSMENTS DURING TREATMENT**

Data is collected weekly for QIDS-A17 to monitor depressive symptoms and suicidality, and BADS-SF, to evaluate changes in the presumed therapeutic processes. See **Table 2** for information regarding which measures are administered at each time point. For these assessments, there is a 7-day time period for data collection.

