#### **9.4 HANDLING OF ADVERSE EVENTS**

Adverse events will be noted by the trial coordinator in a specific log (including date, recorded clinical symptoms, and a brief description of the event). The research team could be notified about adverse events in numerous ways, including through direct (text or telephone) communication with the participant, or at follow-up assessments. Regular meetings (treatment conferences) will be held within the research team where treatment progress and potential adverse events are discussed. Cut-off scores on the suicidal item in QIDS-A17 (self-rated depressive symptoms), might also be indicators of adverse events, and thus be registered in the AE-log. Scores of 2 or 3 points on the suicide item corresponding to a yes to “I think of suicide or death several times a week for several minutes” or “I think of suicide or death several times a day in some detail, or I have made specific plans for suicide or have actually tried to take my life”, will automatically raise a flag in the BASS system, to directly notify members of the research team to follow this up (via the telephone) with the participant.

SAEs will be recorded in the patient’s medical record (Take Care), as well as in the trial coordinator’s log. Appropriate action will be taken in the case of SAE, making sure the participant will get in contact with suitable health care services. Events will be considered as potentially treatment-related up to the 3-month follow-up, where the reporting of adverse events will terminate. The PI will immediately notify the Sponsor of any events of SAE. The PI and sponsor will work together to identify the extent of the SAE and to determine what urgent safety measures are required.

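### No score-based rule is defined for the promised detection of deterioration, and logging of worsening depends on contact that differs by arm

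*Protocol*

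**What the plan says.** Section 6.4.1 describes self-guided I-BA as the guided programme without therapist support. As a safeguard it says that "there will be clinical routines to detect and manage deterioration or suicidal tendencies", and that families will be told how to reach the study team. It does not describe the routines.

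Section 6.5.1 has the QIDS-A17 collected weekly "to monitor depressive symptoms and suicidality". Section 12 says the same for all treatment arms. According to section 5.7.4 the scale "covers the nine DSM-5 symptoms of depression rated in a scale from 0 (none) to 3 (highest) with a sum-range of 0-27", with these bands: "A total score of 6-10 indicates mild depression, 11-15 moderate, 16-20 severe and 21 and above very severe".

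Section 9.4 contains the one rule tied to a score. A 2 or 3 on the suicide item "will automatically raise a flag in the BASS system, to directly notify members of the research team to follow this up" by telephone. The same section says "The research team could be notified about adverse events in numerous ways", naming communication with the participant and the follow-up assessments, and it mentions regular treatment conferences. Section 12 adds weekly conferences with a psychiatrist present.

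Section 9.2 puts increased depressive symptoms first among the expected adverse events and gives the monitoring of adverse events to the therapist. Section 12 says that adverse events are monitored carefully in all three groups.

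**The concern.** Section 6.4.1 names two things to be detected: deterioration and suicidal tendencies. Section 9.4 gives a working rule for the second only. For the first, the protocol states no score, no change from baseline, no named reader of the weekly total and no resulting action.

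Two things are at stake. The first is whether the safeguard exists as described. An adolescent in self-guided I-BA may answer every week and report marked worsening without frequent suicidal thoughts. Whether anyone on the trial team notices then depends on routes with no written criterion.

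The second is the comparison of harms. Section 9.1 counts an increase in a pre-existing symptom as an adverse event. Worsening depression is measured identically each week in every arm, but apart from the suicide item it reaches the log mainly through contact. That contact is typically several times a week in guided I-BA and has no trial-therapist counterpart in the other two arms. The protocol's background asks whether self-guided treatment is possible without loss of efficacy or safety, so a log that depends on contact bears on a central question.

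**Working it through.** **Inputs.** From section 5.7.4: nine symptoms, each scored 0 to 3, with the severe band at 16–20 and the very severe band from 21. From section 9.4: a flag if the suicide item is 2 or 3, so 0 or 1 raises none.

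**1. The plan's own range.** Maximum total = 9 × 3 = 27. This reproduces the stated range of 0–27.

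**2. Highest total without a flag.** Eight other symptoms at 3 and the suicide item at 1: 8 × 3 + 1 = 25. With the suicide item at 0 it is 24. The value of 25 lies 25 − 21 = 4 points above the start of the very severe band.

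**3. Which totals force a flag.** With the suicide item at 0 or 1, every total from 0 to 25 can be reached. The whole severe band (16–20) and 21 to 25 of the very severe band can therefore occur unflagged. Only 26 and 27 cannot occur without a flag.

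**4. How large a rise can go unflagged.** From the top of the moderate band: 25 − 15 = 10 points. From the bottom of the mild band: 25 − 6 = 19 points.

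These are ceilings on what the rule permits. The protocol gives nothing from which to estimate how often such totals would occur, and no frequency is claimed here.

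**5. The monitoring statements by arm.**

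| | Guided I-BA | Self-guided I-BA | TAU |
|---|---|---|---|
| Weekly QIDS-A17 (6.5.1, 12) | yes | yes | yes |
| Suicide-item flag (9.4) | yes | yes | yes |
| Rule on the weekly total | none stated | none stated | none stated |
| Trial therapist, to whom 9.2 gives adverse-event monitoring | yes, contact typically several times a week (6.4.1) | none (6.4.1) | none; care from outside clinics (6.4.2) |
| Careful monitoring claimed (12) | yes | yes | yes |

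The fourth row does not support the fifth in two of the three arms. The measurement is common to all arms, but the main stated route from worsening to the log is not.

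**The case against.** The strongest reply is that section 6.4.1 promises clinical routines and not an automated alarm. Section 9.4 introduces the suicide item as one further indicator among several routes, so it need not be the full content of those routines. This stands in part. A reader might infer that an adolescent could reach 25 points with no alert of any kind, and the documents do not support that. Weekly symptom monitoring, conferences with a psychiatrist present, contact by the family, follow-up assessments and a caregiver QIDS-A17 after five weeks could each bring worsening to light. What these routes lack is a stated score input or a named reader of the weekly total. That is a gap in specification and does not show that scores go unread.

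A reader might also infer that crossing into the severe band turns a participant into someone the trial would have excluded. It does not. Severe MDD at entry is a clinician's DSM-5 judgement (sections 2 and 5.5.1), whereas the QIDS-A17 band is self-reported and is not an entry criterion.

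Nor can it be said that TAU participants are unobserved. They are referred to treating services, and the promise in section 6.4.1 concerns self-guided I-BA.

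Finally, the QIDS-A17 is a secondary outcome analysed by mixed models in all arms (section 8), and the NEQ-20 is collected at post-treatment and three months, so the log is not the only view of harm. That is true. But a comparison of mean trajectories does not count the individuals who worsened, and it does not remove the imbalance in the log itself.

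**Conclusion.** The point holds in a limited form. The protocol promises detection of deterioration but defines no automatic or score-based alert for it. Any QIDS-A17 total up to 25 of 27 can pass without a flag, including 21 to 25 in the very severe band. Sections 9.2 and 12 also do not fit together for the arms without a trial therapist.

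Counts of increased depressive symptoms in the log can therefore differ by arm because of how events come to notice. If more contact leads to more logging, guided I-BA would appear to have more such events than the other arms at the same true rate. That direction is an assumption, and its size cannot be estimated from the document.

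The conclusion rests on the protocol alone. If the clinic's routines specify how the weekly total is read, the protocol should say so. This should be corrected, but because other safeguards are described it does not show the trial to be unsafe.

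**What to change.** - Reconcile sections 6.4.1, 6.5.1, 9.2, 9.4 and 12. State who reads the weekly QIDS-A17 total in the arms without a trial therapist and how the promised detection of deterioration works. Otherwise withdraw the statement that deterioration is detected. Whether there is a threshold or action, and what it is, is for the trial's clinicians; none is proposed here.
- For the safety comparison, count and report worsening in all three arms from the same weekly QIDS-A17 data under one common definition. Present this beside the adverse-event log and keep it subject to the case assessment in section 9.3. Because weekly ratings run only during treatment while adverse-event reporting continues to the three-month follow-up, state which period the count covers.
- Fix the definition before outcome data are analysed. Section 6.6.2 places that analysis after primary-endpoint data collection is complete.

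The cost is small, since the data are already collected: a little more data review and reporting. The count of recorded worsening in the self-guided and TAU arms is likely to rise, and the report should explain that this reflects even ascertainment.

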#### 6.4.2 TREATMENT AS USUAL (TAU)

Our control condition represents treatment as usual. Participants randomised to TAU, will be referred to the local CAMHS or primary care unit for children and youths and will be free to receive any treatment, either psychosocial, medical or the combination of both. The

content of TAU and the treatment techniques used, will be collected by clinician-interview with the caregiver at 3-months follow-up.

#### **6.4.3 THERAPIST TRAINING, SUPERVISION AND MONITORING**

All therapists will receive training before the trial starts. They will be introduced to the use of the platform and the I-BA protocol during a one-day training by the treatment constructor ([name]). Regular supervision will be held to discuss treatment progress for individual patients and follow up on clinical needs and potential adverse events. Protocol violations will be recorded.

### **6.5 SUBSEQUENT ASSESSMENTS**

#### **6.5.1 ASSESSMENTS DURING TREATMENT**

Data is collected weekly for QIDS-A17 to monitor depressive symptoms and suicidality, and BADS-SF, to evaluate changes in the presumed therapeutic processes. See **Table 2** for information regarding which measures are administered at each time point. For these assessments, there is a 7-day time period for data collection.

